#### Safety:

Safety analysis will be conducted for the whole study population as well as for the five treatment groups separately. AEs and SAEs will be reported with absolute and relative frequencies per treatment group along with the corresponding 95% CIs (two-sided). Differences between different groups (each of the dose regimens separately) will be compared using Chi-squared Test. For all comparisons 95% CIs (two-sided) will be provided.

#### Pharmacokinetic and pharmacogenetic analysis:

Pharmacokinetic analysis will be performed for the complete study population. Differences between different groups and patients will be compared using Chi-squared Test. For all comparisons 95% CIs (two-sided) will be required.

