| PK assessments        | Samples for dobutamine will be taken at 60 min and 180 min after the allocated dose had time to enter the systemic circulation. In the case the targeted PD effect is reached with a different dose, the second PK sample will be withdrawn 180 min after effective dose infusion.                                                                                                                                                                                                                                                                                                                                                                                                                                                                                                                                                                                                                                                                                                                                                                                                                                                                                                                                                                                                                                                                                                                                                                               |        |        |        |        |        |        |                        |   |     |    |      |    |              |    |    |    |    |    |              |   |   |    |   |   |

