infusion rates (0.5 to 20 µg/kg/min) (18, 31-33). In 27 children in intensive care with age ranging between 1 month and 16.6 years, the pharmacokinetics of dobutamine was found to follow a 1 or a 2-compartment model and was characterized by a considerable inter-individual variability: for an administration rate of 5 µg/kg/min, steady-state concentrations ranged between 3.79 and 400 ng/ml (34). Age, body weight, and sex were not related to the value of the PK parameters. In neonates, no association was found between plasma clearance and birth weight or gestational age (18).

Dobutamine was found to obey a threshold model, which consists in a lack of response when dobutamine concentration is below a threshold value, and, beyond this threshold, to a linear increase in the response for logarithmic increases in plasma dobutamine concentration (18, 31-33). However, the inter-individual variability in the cardiovascular response to dobutamine administration is high. Several studies have shown that different genetic polymorphisms may be related to this inter-individual variability, determining success or failure of circulatory therapy (50-52). We aim to analyse the pharmacogenetics of GNAS1 and β1-adrenoceptor polymorphism and different enzymes: COMT, MAO-A, MAO-B, because they are the main metabolizer enzymes of dobutamine.

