| 
 
To determine the individual variables that explain the interindividual pharmacokinetic (PK)/PD variability.
 
 | 
 
To determine the correlation between PK and PD.
 
 
[A] The effective start of the infusion (t0) will be calculated as the time at which the infusion pump is switched on plus the empirical value for the interval arising from the dead space. We summarize t0 as “the time at which dobutamine is expected to reach the circulation”
 
[B] Acceptable haemodynamic status is defined, for the purposes of this study, as the achievement and maintenance of dose success during the first 72 h from birth. The loss of such acceptable haemodynamic status occurs whenever there is a change in therapeutic strategy that involves cardiovascular treatment other than dobutamine alone due to exceeded safety parameters, treatment failure of the investigational infusion or the need for rescue treatment or death; any additional fluid bolus is considered as cardiovascular treatment.
 |
|---------------------------------------------------------------------------------------------------------------------------------------------------------------|----------------------------------------------------------------------------------------------------------------------------------------------------------------------------------------------------------------------------------------------------------------------------------------------------------------------------------------------------------------------------------------------------------------------------------------------------------------------------------------------------------------------------------------------------------------------------------------------------------------------------------------------------------------------------------------------------------------------------------------------------------------------------------------------------------------------------------------------------------------------------------------------------------------------------------------------------------------------------------|

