### 4.2 SCIENTIFIC RATIONALE FOR STUDY DESIGN AND DOSE

As other catecholamines, dobutamine is always administered in continuous i.v. infusion, preferably through a central line.

Recent data from clinical and pre-clinical investigations, and clinical experience, indicate that dobutamine can be safely up titrated from a starting dose of 5 µg/kg/min in steps of 5 µg/kg/min in rather flexible timing within limits of up to 20 µg/kg/min; and that there is until now no evidence that dobutamine could introduce harm in newborn babies using this treatment scheme (11, 28, 41).

Although the information is scarce, there is a wide range in threshold doses of dobutamine needed to increase heart rate, blood pressure or cardiac output in children and adolescents (31-33), so that individual titration is extremely important. The minimum dobutamine dose at which a pharmacodynamic effect has been shown in neonates is 10 µg/kg/min (15-17, 19, 23, 25, 26,

28). In two RCT conducted in preterm infants on the effect of dobutamine on SVC flow (11, 28), the lowest dobutamine dose that was evaluated was 10 µg /kg/min.

Results from PK sub-study NeoCirc-001A revealed high inter-individual PK variability regarding dobutamine elimination half-life and consequently, time to reach steady-state that ranged from 15 min to 180 min (35). Due to this important inter-individual variability, there is still a need to confirm the lower effective dose in very preterm neonates; therefore, the proposed study will cover dobutamine dose-range from 5 to 20 µg /kg/min.

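### The protocol names only a chi-squared test for comparing pharmacokinetics, but the data are continuous, paired concentrations and the endpoint is a PK/PD correlation

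*Protocol*

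**What the plan says.** Section 9.1.2 of the protocol treats pharmacokinetics and pharmacogenetics together in three sentences. On the population: "Pharmacokinetic analysis will be performed for the complete study population". On the method: "Differences between different groups and patients will be compared using Chi-squared Test". On precision: "For all comparisons 95% CIs (two-sided) will be required". Section 9 names no other method for PK and defines no categories of PK result.

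Section 3 sets the secondary objective that this analysis serves: "To determine the individual variables that explain the interindividual pharmacokinetic (PK)/PD variability". The matching endpoint is "To determine the correlation between PK and PD".

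The synopsis describes the data: "Samples for dobutamine will be taken at 60 min and 180 min" after the allocated dose has had time to reach the circulation. If the target effect is reached at another dose, the second sample is timed from that dose. Sections 8.1.1.4 and 8.1.1.5 place the SVC flow assessments at the same two visits.

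Section 9.1.3 states the protocol's own convention for baseline data: t-tests for numerical variables and chi-squared for categorical ones.

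**The concern.** A Pearson chi-squared test compares counts of independent subjects across categories. A plasma concentration is a measurement, and each infant gives up to two. The named test therefore has nothing to work on unless concentrations are first cut into classes, and the protocol sets no cut-points. Nor does a test of group differences produce a correlation, a slope or a ranking of explanatory variables, which is what Section 3 asks for.

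A statistical analysis plan that used a suitable method would have to depart from the protocol text, while one that followed the text would choose cut-points that nobody had fixed in advance. Each PK sample costs a very preterm infant one millilitre of blood (Sections 8.1.1.4 and 8.1.1.5), so the method named for those samples should be able to use them.

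**Working it through.** The protocol gives no sample size, power or error rate for the PK analysis, so there is no figure of its own to reproduce. The check is whether the named test fits the data.

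**Inputs**
- Maximum of 30 infants, expected as 5, 9, 12, 4 and 0 over the five doses (Section 9.1.1). These add to 5 + 9 + 12 + 4 + 0 = 30.
- Two samples per infant, at 60 and 180 minutes (synopsis).
- The measurement scale is ng/ml. The background illustrates it with "steady-state concentrations ranged between 3.79 and 400 ng/ml" at one infusion rate (Section 2.2.2).

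**1. Concentrations as measured.** Take one time point, with 30 distinct values and the g = 4 dose groups expected to hold infants. The table is 4 × 30 with one infant in each column.
- Statistic = n(g − 1) = 30 × 3 = 90.
- Degrees of freedom = (30 − 1)(4 − 1) = 87.
- p = 0.39.
- Largest expected count = 12 × 1/30 = 0.4.

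These results do not depend on the concentrations. Any set of 30 distinct values gives the same statistic and p-value, so the test carries no information.

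**2. Concentrations cut at the median.** This split is an assumption made here for the check. Expected counts per cell are half of each group:

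| Dose (mcg/kg/min) | n | Expected per cell |
|---|---|---|
| 5 | 5 | 2.5 |
| 7.5 | 9 | 4.5 |
| 10 | 12 | 6.0 |
| 12.5 | 4 | 2.0 |

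Three of the four groups are below 5. If the fifth group holds its expected 0 infants, its row has zero expected counts and the five-group test cannot be computed unless that row is dropped.

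**3. Both samples together.** With two samples, 30 infants give up to 60 values. Values from the same infant are not independent, so pooling them breaks the assumption of the test. After a dose change, the second value no longer belongs to the allocated dose group.

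**4. Differences between patients.** If this means individual infants, one or two measurements each give no table of counts.

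**5. Objective against method.** Section 3 asks for explanatory variables and a correlation. A chi-squared test of group differences yields a p-value for association between categories and neither of these.

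**6. Illustration of the loss (assumed inputs).** The simulation ran 4,000 trials with groups of 5, 9, 12 and 4 and one concentration per infant, proportional to dose. The between-infant SD of log concentration is not in the protocol, so a range is shown. Power at the 5% level to detect that concentration differs by dose:

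| Log SD | Median-split chi-squared | ANOVA on log concentration | Regression on log dose |
|---|---|---|---|
| 0.3 | 81% | 99% | over 99% |
| 0.5 | 39% | 69% | 87% |
| 0.8 | 17% | 30% | 48% |
| 1.0 | 12% | 20% | 33% |

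The regression is favoured because it matches the assumed truth. The finding does not rest on this table.

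**The case against.** The strongest reply concerns scope. The sentence stands under a joint heading with pharmacogenetics, and a chi-squared or exact test of genotype against response (yes/no) is a valid type of test that serves the objective directly. This stands, and the test should be kept for that use. It does not extend to the concentrations. The wording about patients may also mean patient subgroups rather than individual infants. Even so, a concentration compared between subgroups is still not a count.

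A second reply is that models for correlation and covariates are commonly left to a statistical analysis plan. This is right as far as omission goes. The point here is that the protocol does name a method for PK, and that method does not fit.

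Several stronger readings are tempting, and the protocol does not support them:
- **That the PK/PD objective cannot be met at all.** Concentration and SVC flow are both collected at 60 and 180 minutes, and nothing forbids a correlation. The data suffice; the named test does not.
- **That categorising discards most of the information.** For a normal variable split at the median, the large-sample share retained is 2/π = 64%, so about 36% is lost.
- **That the samples are often taken at two doses.** The planned numbers and efficacies give 5 × 0.45 + 9 × 0.70 + 12 × 0.80 + 4 × 0.90 = 21.75 expected successes at the allocated dose. About 8 of 30 infants might then change dose for non-response, plus an unknown number for other reasons.
- **That concentrations here are right-skewed over a 105-fold range (400/3.79).** That range comes from 27 children in intensive care aged 1 month to 16.6 years. No distribution is given for preterm infants.
- **That 60-minute levels cannot be compared.** Section 4.2 reports "time to reach steady-state that ranged from 15 min to 180 min". Assume that steady state takes 3.3 to 5 half-lives. The 60-minute level is then 53% to 69% of steady state at the slow extreme, but above 99.9% at the fast extreme. This is a reason to include sampling time in the model. It does not make the samples unusable.

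**Conclusion.** The method is wrong as written for PK. A chi-squared test cannot be applied to continuous concentrations, paired within infant, without categories that the protocol does not define. It does not give the correlation or the explanatory variables in Section 3, and it departs from the convention in Section 9.1.3. This conclusion needs no outside figure, since it follows from the type of data and from the statistic staying at 90 on 87 degrees of freedom whatever the concentrations. The expected counts of 2.0 to 6.0 assume the planned allocation and a median split, and the power figures assume a log SD of 0.3 to 1.0.

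The reach is limited. One secondary objective is affected, while the primary dose-finding analysis, the allocation and the sample size are not. The genotype-by-response use of a categorical test remains valid. A reader might infer that a full population PK or threshold model is required. It is not: with at most 30 infants and two samples each, such a model is an option that depends on identifiability.

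**What to change.** Replace the chi-squared sentence in Section 9.1.2 with three statements.

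1. **PK.** Analyse log concentration by regression or a mixed model on log infusion rate (the rate running at sampling) and sampling time since t0, with a random infant effect and a small set of pre-specified covariates. The number of covariates should respect at most 30 infants. Their choice should take account of Section 2.2.2, which reports no association of neonatal clearance with birth weight or gestational age. A population PK model may be named as an option if it is identifiable.
2. **PK/PD.** Report the correlation or slope of SVC flow on log concentration with a two-sided 95% CI, allowing for two observations per infant.
3. **Pharmacogenetics.** Keep a categorical test, preferably exact given n of at most 30, for genotype against response (yes/no).

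The cost is a short text change and some extra analysis work. No further samples, visits or infants are needed.

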### 9.1.3. Baseline Descriptive Statistics

Demographic and baseline variables will be recorded for each group with mean, median and standard deviation for numerical variables and absolute and relative frequencies for categorical variables. Variables will be compared descriptively between each of the five dose regimen groups with mean differences and t-tests and rate differences and Chi-squared test respectively. 95%-confidence intervals (CIs) will be provided.

## 10. SUPPORTING DOCUMENTATION AND OPERATIONAL CONSIDERATIONS

### 10.1. REGULATORY, ETHICAL, AND STUDY OVERSIGHT CONSIDERATIONS

#### 10.1.1. Informed Consent Process

##### 10.1.1.1 Consent and Other Informational Documents Provided to participants

Consent forms describing in detail the study agent, study procedures, and risks are given to the parent/ patient's legally acceptable representative and written documentation of informed consent is required prior to starting intervention/administering study product.

##### 10.1.1.2 Consent Procedures and Documentation

The Investigator (according to applicable regulatory requirements), or a person designated by the Investigator (must be suitably qualified and experienced), and under the Investigator's responsibility, should fully inform the parent/ patient's legally designated representative of all pertinent aspects of the clinical trial, including the written information given approval/favourable opinion by the Ethics Committee.

Prior to a patient's participation in the clinical trial, the written ICD should be signed, name filled in and personally dated by the parent/ patient's legally designated representative, and by the person who conducted the informed consent discussion. A copy of the signed and dated written ICD will be provided to the patient. The original signed form will be retained at the study site. As discussed on sections 5.1 and 5.3, deferred informed consent may apply to this trial and the ICD signed *a posteriori*, whenever the clinical situation is considered an emergency and the statements on *Article 35 of the Regulation of the European Union on Clinical Trials (Regulations (EU) no536/2014)* (see above, section 5.1) are fulfilled.

The parent/ patient's legally designated representative will be allowed as much time as wished to consider the information, and the opportunity to question the investigator or other independent parties to decide whether they will participate in the study; and must have the appropriate information presented in an understandable way and in a format suitable to their needs.

---

#### 10.1.2 Study Discontinuation and Closure

The study may be temporarily discontinued or prematurely terminated if the sponsor judges it necessary for medical, safety, regulatory, or other reasons consistent with applicable laws, regulations, and good clinical practice.

Circumstances that may warrant termination or suspension include, but are not limited to:

- Determination of unexpected, significant, or unacceptable risk to participants
- Demonstration of efficacy that would warrant stopping
- Insufficient compliance to protocol requirements
- Data that are not sufficiently complete and/or evaluable
- Determination of futility

Study site participation may be discontinued if the investigator, or the ethical review board of the study site judges it necessary for any reason.

---

#### 10.1.3 Confidentiality and Privacy

The study staff will ensure that the participant's anonymity is maintained. The participants will be identified only by a participant code on the eCRF and any electronic database.

All documents will be stored securely and only accessible by study staff and authorized personnel.

Applicable regulations for storage, transmittal and disclosure of patient information will be always followed. The study will comply with the Data Protection Legislation.

Following formal admission to the study, patient data will be recorded in the hospital case record in the usual way including the circumstances of their entry to the study. Additionally, data will be held in case report forms (eCRF). These files will be identified by a study code, date of birth and participant code only.

Results of the study may be communicated at scientific meetings and will contribute to the scientific literature. At no time, will this be done in such a way that an individual patient may be identified.

---

#### 10.1.4 Quality Assurance and Quality Control

The designee will implement and maintain quality control and quality assurance procedures with written standard operating procedures to ensure that the study is conducted and data are generated, documented, and reported in compliance with the protocol, ICH GCP, and applicable regulatory requirements.

QC procedures will be implemented beginning with the paper based primary study documentation that will be entered into the electronic data entry system by generating data QC checks on the database (edit checks).

Training for the study will be provided at the Study investigator's meeting (if applicable) and for site personnel prior to the initiation of study

The investigational site will provide direct access to all trial related sites, source data/documents, and reports.

### **Serious Breaches**

A serious breach is defined as “A breach of GCP if applicable or the study protocol which is likely to effect to a significant degree –

- (a) The safety or physical or mental integrity of the subjects of the study; or
- (b) The scientific value of the study.

Any serious breaches will be notified to the competent Regulatory Authority according to applicable legislation.

### **Study file**

The Investigator must maintain confidential all study documentation and take measures to prevent accidental or premature destruction of these documents. It is recommended that the Investigator retain the study documents at least twenty-five years after the completion or discontinuation of the Clinical Trial.

## 10.2.ABBREVIATIONS

|      |                                                                                   |
|------|-----------------------------------------------------------------------------------|
| AE   | Adverse Event                                                                     |
| AR   | Adverse reaction                                                                  |
| AUC  | Area under the curve - or under the receiver operating characteristic curve (ROC) |
| BE   | Base excess                                                                       |
| BP   | Blood Pressure                                                                    |
| bpm  | beats per minute                                                                  |
| BW   | Body Weight                                                                       |
| CI   | Confidence Interval                                                               |
| CMV  | Continuous mandatory ventilation                                                  |
| CMP  | Clinical Monitoring Plan                                                          |
| CPAP | Continuous positive airway pressure                                               |
| CPC  | Clinical Publication Committee                                                    |
| CRF  | Case Report Form                                                                  |
| CRP  | C reactive protein                                                                |
| CRT  | Capillary refill time                                                             |
| cUS  | Cranial ultrasound                                                                |
| DSMB | Data Safety Monitoring Board                                                      |
| EDC  | Electronic Data Capture                                                           |

|                  |                                                            |
|------------------|------------------------------------------------------------|
| EC               | Ethics Committee                                           |
| Echo-D           | Echocardiography-Doppler                                   |
| eCRF             | Electronic Case Report Form                                |
| EFCNI            | European Foundation for the Care of Newborn Infants        |
| EMA              | European Medicines Agency                                  |
| EudraCT          | European Union Drug Regulating Authorities Clinical Trials |
| EoT              | End of Treatment                                           |
| GA               | Gestational Age                                            |
| GCP              | Good Clinical Practice                                     |
| Hb               | Haemoglobin                                                |
| HFNC             | High flow nasal cannula                                    |
| HFOV             | High frequency oscillatory ventilation                     |
| HULP             | La Paz University Hospital                                 |
| ICD              | Informed Consent Document(s)                               |
| ICH              | International Conference on Harmonisation                  |
| IMP              | Investigational Medicinal Product                          |
| ITT              | Intention-To-Treat                                         |
| IVH              | Intraventricular haemorrhage                               |
| MABP             | Mean Arterial Blood Pressure                               |
| MedDRA           | Medical Dictionary for Regulatory Activities               |
| NICU             | Neonatal Intensive Care Unit                               |
| NIRS             | Near-Infrared Spectroscopy                                 |
| NS               | Normal saline                                              |
| OR               | Odds Ratio                                                 |
| pCO 2 | Partial pressure of carbon dioxide                         |
| PD               | Pharmacodynamic(s)                                         |
| PDA              | Patent Ductus Arteriosus                                   |
| PI               | Principal Investigator                                     |
| PK               | Pharmacokinetic(s)                                         |
| PMA              | postmenstrual age                                          |
| RCT              | Randomised controlled trial                                |
| ROC              | Receiver operating characteristic                          |
| ROP              | Retinopathy of prematurity                                 |
| SAE              | Serious adverse event                                      |
| SAR              | Serious adverse reaction                                   |
| RVO              | Right Ventricular Output                                   |
| SaO 2 | Arterial oxygen saturation                                 |
| SAE              | Serious Adverse Event                                      |
| SAR              | Serious adverse drug reaction                              |
| SERMAS           | Servicio Madrileño de Salud (Madrid, Spain)                |
| SNAPPE-II        | Score for Neonatal Acute Physiology Perinatal Extension    |
| SoA              | Schedule of Activities                                     |
| SOP              | Standard Operating Procedure                               |
| SpO 2 | Pulse oximetry                                             |
| SUSAR            | Suspected unexpected serious adverse reaction              |
| SVC              | Superior Vena Cava                                         |
| TMF              | Trial Master File                                          |
| TSC              | Trial Steering Committee                                   |

|             |                                                                         |
|-------------|-------------------------------------------------------------------------|
| UCICEC      | Central Research and Clinical Trials Unit                               |
| UCICEC-HULP | Central Research and Clinical Trials Unit at La Paz University Hospital |

